### Study organization

The study will be supervised for data collection, security, and storage by the Department of Anesthesiology, the First Affiliated Hospital of Zhengzhou University, and [name] and [name] will be in charge of data quality control. The institutional ethics committee from our hospital will be involved in the whole process of the trial.

### Trial interventions

All patients will receive the standard multidisciplinary team service (including the senior obstetrician, gynecologist, anesthesiologist, neonatology teams, urologist, imaging doctor, and adequate number of blood units in the operating room). The antepartum diagnosis of PA is made clinically, based on the pelvic ultrasound or MRI. Pregnant woman with PA diagnosed by ultrasound or MRI will be recruited in this study. In both groups, pregnant woman will undergo the standard protocol, as described previously [14]. Considering the risk of massive bleeding complicated by profound hypotension and coagulopathy, we choose general anesthesia for all patients with PA [17, 18]. Endotracheal intubation is performed with the use of a rapid sequence induction (RSI) technique [19, 20]. We monitor invasive arterial blood pressure (ABP), electrocardiogram (ECG), SPO_2_, PetCO_2_, temperature (T), arterial blood gas (ABG), and thrombelastograph (TEG) of the patients during the operation. After fetal delivery and umbilical cord clamping, according to the PA location and depth, patients are given local excision of the uterine wall, placenta evacuation, partial cystectomy, and bladder repair. 20 U of oxytocin and 250 μg of tromethamine are injected in the myometrium.

In the traditional group, patients are given a cesarean section without AABO. In this group, conservative treatments for PA, including oversewing of the placental bed, a uterine tamponade, and bilateral uterine artery, ligation are used. Hysterectomy is performed when massive hemorrhage cannot be controlled.

In the interventional group, the cesarean section and all endovascular procedures will be performed in a hybrid operation room equipped with a digital subtraction angiography (DSA) machine (Allura Xper FD20, Philips, Best, the Netherlands). Interventional radiologists will select the proper diameter of the balloon, which is measured by MRI, and insert a 5 F pigtail catheter (Cook, Bloomington, IN, USA) into the abdominal aorta at the level of T12 with an 8-F sheath (Cook) from the right femoral artery at the groin, with the patient under local anesthesia. Next, 5 ml iodixanol (Visipaque-320, Nycomed, Oslo, Norway) will be injected to locate the origin of the renal arteries. An 8-F, 40 × 14 mm, 40 × 16 mm, or 40 × 18 mm balloon catheter (Bard Peripheral Vascular, Tempe, AZ, USA) will be inserted into the infrarenal abdominal aorta and fixed carefully. Each patient will have peripheral oxygen saturation placed on the great toes of the left foot to allow the interventional radiologist to determine when balloon catheter occlusion of the aorta has occurred during the endovascular procedures. Indirectly confirmed balloon block effective indicators are as follows: the digit blood oxygen is reduced to zero, the blood oxygen curve is at a flat state, and the bipedal arterial blood pressure drops to zero [13, 21]. A sketch drawing of the abdominal aortic balloon position and related monitoring of physiological parameters during the operation is shown in Fig. 2.

**Fig. 2 Fig2:**
[figure not shown]
Sketch of abdominal aortic balloon position and related physiological parameter monitoring

Temporary aortic balloon occlusion will be implemented by using 10–16 ml of saline solution immediately after fetal delivery and umbilical cord clamping. The balloons are inflated for 12–15 min, and the inflations are alternated with deflations of 1–2 min. As reported, it is safe to block the pelvic organs and lower limbs for 30 min [22]. After the operation, a pelvic angiography is performed again. If there is active bleeding, uterine artery embolization (UAE) is supplemented. The fluoroscopy time is recorded in all cases. When the operation is completed, the catheter is pulled out and compression bandaging of the femoral artery puncture sites is performed. The lower limbs of the patients are massaged after the operation. Low-molecular-weight heparin is given to the patients after 24 h to prevent vein thrombosis of the lower limbs.

### Data collection

#### Primary outcome

The primary outcome is estimated blood loss (EBL). EBL is measured with reference to the collected blood in the suction bottle in the operating room and to the weight of the surgical swabs, excluding the volume of amniotic fluid.

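### Operating time leaves out procedures that only the AABO arm has, and blood loss and hysterectomy have no common follow-up window that would show whether bleeding was prevented or postponed

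*Protocol article*

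**What the plan says.** All references are to the protocol article, Methods/design.

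- **Primary outcome.** EBL is "measured with reference to the collected blood in the suction bottle in the operating room" and by swab weight, with amniotic fluid excluded. No start or stop time is given.
- **Secondary outcomes.** Cesarean hysterectomy is counted if it occurs during delivery; the abstract calls it the most important secondary outcome. Operating time runs from incision of the skin to closure of the abdomen. Transfusion volume (no stop time), ICU stay and total hospital stay are also listed. Embolisation and re-operation are not.
- **Trial interventions, AABO arm.** Sheath and catheters are inserted through the femoral artery under local anesthesia, and the balloon is first inflated at cord clamping. Then: "After the operation, a pelvic angiography is performed again. If there is active bleeding, uterine artery embolization (UAE) is supplemented". On location, "the cesarean section and all endovascular procedures will be performed in a hybrid operation room".
- **Trial interventions, control arm.** "In the traditional group, patients are given a cesarean section without AABO". Oversewing, tamponade and arterial ligation are described, with hysterectomy if bleeding cannot be controlled. No angiography or embolisation is described.

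**The concern.** AABO interrupts pelvic flow for a limited time, and the protocol itself foresees that some women will still be bleeding when the operation is over. Bleeding that appears late is therefore a failure that a fair comparison should be able to detect. As written, a hysterectomy done later does not meet the outcome definition, an embolisation done to stop bleeding enters no listed outcome, and blood lost after suction and swab collection ends is not measured. Operating time has a separate problem: its two limits exclude work that belongs to one arm only. At stake are a procedure-time comparison tilted towards AABO by its definition, and a statement of benefits and risks that lacks the late events needed to judge the technique.

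**Working it through.** **Step 1. Set the outcome limits beside the events the protocol describes.**

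| Event | Arm in which it is described | Where it is counted |
|---|---|---|
| Sheath and balloon placement | AABO only | Very probably not in operating time: done under local anesthesia and needed by cord clamping, though its order relative to incision is not stated |
| Bleeding during surgery, including during deflations | Both (deflations AABO only) | EBL |
| Angiography after the operation | AABO only | Not in operating time |
| Embolisation for active bleeding | AABO only | Not in operating time; not an outcome |
| Blood loss after suction and swab collection ends | Possible in both | Not in EBL; perhaps indirectly in transfusion volume or length of stay |
| Hysterectomy or re-operation after delivery | Possible in both | Not in the hysterectomy outcome; re-operation is not an outcome |

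**Step 2. Operating time.** Let P be placement time before incision, S incision-to-closure time, and A the time for angiography and embolisation after closure. Total procedure time is P + S + A in the AABO arm and S in the control arm, where P = A = 0 as described. The plan compares S alone. The recorded difference (AABO minus control) is therefore the difference in total procedure time minus the mean of P + A. Because P + A cannot be negative, the omission can only flatter AABO. The protocol gives no minutes for P or A.

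**Step 3. Blood loss.** Let L(AABO) and L(control) be mean loss after collection ends. Then

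measured difference (control − AABO) = difference in total loss + x, where x = L(AABO) − L(control).

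The document gives neither L, so both the sign and the size of x are unknown. If x > 0, measured EBL overstates the benefit; if x < 0, it understates it.

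**Step 4. The plan's own figure, and what x would do to it (illustration only).** Sample size gives an expected difference of 1000 ml, SD 355 ml, a clinically important difference of 800 ml, a 2.5% level and 90% power. Read as superiority by an 800 ml margin:

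n = 2 × [355 × (1.960 + 1.282) / (1000 − 800)]² = 66.2, so 67 per group, as stated. With 20% dropout, 67 / 0.80 = 83.75, so 84, against 85 stated.

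On that reading there are 200 ml to spare above the margin. The standard error at 67 per group is 355 × √(2/67) = 61.3 ml. Suppose measured EBL shows the full 1000 ml and the SD stays at 355 ml. Power of a margin test on *total* loss is then Φ[(200 − x)/61.3 − 1.960]:

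- x = 0: 90.3%
- x = 25 ml: 81.4%
- x = 50 ml: 68.6%
- x = 100 ml: 37.1%

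The values of x are assumptions. The Statistics section names Student's t test and states no margin. Against zero, power at 67 per group stays near 100% for true differences of 850 to 1000 ml. Under that test a positive x would inflate the estimated effect but would not put the significance result in doubt.

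**The case against.** The strongest reply is that the primary outcome is not shown to be biased, and most of it stands.

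- A reader might infer that every outcome clock stops at the end of surgery. Only operating time has an explicit clock of that kind. EBL is bounded by method and place, and that place is the hybrid room in which angiography and embolisation are also done. Blood lost then might be collected. This still leaves a gap: without a stated end point, collection could run longer in one arm than in the other.
- A reader might infer that all bleeding after deflation is lost. That is not so: "The balloons are inflated for 12–15 min, and the inflations are alternated with deflations of 1–2 min", and bleeding during those deflations, or after any deflation before closure, is intraoperative and collected.
- A reader might infer that EBL and hysterectomy are biased towards AABO. The same definitions apply to controls, who may also bleed or need hysterectomy later, and embolisation might reduce later loss in the AABO arm.
- Transfusion volume, ICU stay, hospital stay and adverse-event reporting may reflect some late bleeding. They do so only indirectly, and none identifies a re-intervention.
- Incision-to-closure is a clear measure, applied identically in both arms, of how long surgery takes. That is fair, but it does not measure the time the AABO strategy takes, and nothing else listed does.
- An article may leave collection windows to the full protocol. That excuses the missing EBL end point in part. It does not excuse the hysterectomy and operating-time limits, which the article itself sets.

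**Conclusion.** The point holds for operating time, and as a gap in outcome coverage for the rest.

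- **Operating time** under-records the AABO procedure. The omission is the whole of the post-operative angiography and any embolisation, taking after the operation to mean after abdominal closure, and very probably catheter placement, assuming it precedes incision. The direction is clear; the minutes are not given.
- **Hysterectomy, embolisation and EBL.** The restriction to delivery, the absence of embolisation from the outcomes, and the lack of a common EBL end point mean that the plan cannot tell bleeding prevented from bleeding postponed.

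The document does not support the stronger claim that measured blood loss or hysterectomy favours AABO: it gives no post-operative loss or event rate for either arm. Nor do the power figures above show a loss of power in the stated analysis, since they rest on assumed values of x and on a margin test that the Statistics section does not specify. This is a worthwhile, inexpensive improvement, not a flaw that invalidates the primary comparison.

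**What to change.** These are changes to measurement and reporting only; none alters treatment.

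1. Report total procedure time, from first puncture or incision (whichever comes first) to the end of the last procedure, beside incision-to-closure time, in both arms.
2. Count hysterectomy, embolisation and re-operation for bleeding from delivery to discharge in both arms, and list them as secondary outcomes. Hysterectomy during delivery can still be reported separately.
3. State one end point for EBL collection that applies to both arms, and say whether blood collected during the angiography falls inside it.
4. Report measured loss to 24 h in both arms as a supportive secondary outcome. It should not be a condition for the superiority conclusion, because that would in effect make it a co-primary outcome with no sample-size basis.

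The cost is a few extra chart and theatre-log fields. The drawback is that 24 h loss is noisier than intraoperative loss, which is a further reason to keep it supportive. The Trial status section says that recruitment had not started at publication, so on that statement all four could be fixed before any data are collected.

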#### Secondary outcomes

The following are the secondary outcomes of interest in the study:Occurrence of cesarean hysterectomy (CH) during deliveryBlood transfusion volumeNeonate outcome: 1, 5 and 10 min Apgar scoresOperating time from the time of skin incision to abdominal closureBalloon occlusion-relative data: balloon occlusion time, fetal radiation doseBalloon occlusion-relative complications: vascular aneurysm, dissection or rupture, arterial embolismLength of stay in intensive care unit (ICU)Total hospital stay

### Patient withdrawal

A participant or a patient’s relative who no longer agrees to participate in the study can withdraw at any time without need of further explanation. Patients who are withdrawn from the study protocol will not be followed up, and their data will not be analyzed. It is essential for the trial to collect as much data from each participant as possible.

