### Sample size

The sample size was calculated to compare two proportions with two-sample noninferiority or superiority. According to Muñoz et al., median blood loss was 2000 ml in parturients with PA during delivery [23]. The study of Panici et al. showed that median blood loss was 950 ml in parturients with AABO at cesarean section [24]. Considering a difference in volume of bleeding of 1000 ml with a standard deviation of 355 ml [13] in two treatment groups, a difference of 800 ml between two treatment groups is considered to be clinically important. Assuming the difference between two groups at a 2.5% significance level and a power of 0.90, 67 patients in each group are required for a comparison within the groups. Considering an estimated 20% dropout rate, 85 patients in each group for a total of 170 patients will be included in this study.

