### Statistics

An intention-to-treat analysis will be performed to compare all primary and secondary outcomes in the future study. Continuous variables will be described as means ± standard deviation (SD). Categorical variables will be described as percentages. Demographic data, blood transfusion volume, operating time, length of stay in the ICU, total hospital stay, and EBL will be analyzed by Student’s *t* test to compare the two methods. The occurrence of CH during delivery will be compared by the chi-square test. The neonate Apgar scores will be analyzed using the Mann-Whitney *U* test.

The statistical analyses will be carried out with SPSS software (SPSS, Inc., Chicago, IL, USA). The statistical significance will be considered with a two-tailed *P* value <0.05 and a one-tailed *P* value <0.025.

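### The withdrawal rule discards data from withdrawn randomised patients, which contradicts the declared intention-to-treat analysis of all outcomes

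*Protocol article*

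**What the plan says.** The protocol article makes four statements that bear on who is analysed.

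- **Patient withdrawal.** A participant or a relative who no longer agrees to take part "can withdraw at any time without need of further explanation". The section continues: "Patients who are withdrawn from the study protocol will not be followed up, and their data will not be analyzed". Its last sentence points the other way: "It is essential for the trial to collect as much data from each participant as possible".
- **Statistics.** "An intention-to-treat analysis will be performed to compare all primary and secondary outcomes in the future study".
- **Sample size.** "Considering an estimated 20% dropout rate, 85 patients in each group for a total of 170 patients will be included in this study". The number before this allowance is 67 per group.
- **Primary outcome and Secondary outcomes.** EBL is taken from suction bottles and weighed swabs at operation. Hysterectomy is counted during delivery, operating time ends at abdominal closure, and the last Apgar score is at 10 minutes.

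The section on randomization, allocation concealment and blinding describes how the list is generated and concealed. It describes no masking of patients, surgeons or the staff who measure EBL.

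**The concern.** An intention-to-treat analysis keeps every randomised patient in the assigned arm. A rule that drops all data from withdrawn patients, including data already recorded, defines a different population. An analyst who follows one section breaches the other, so a separate analysis plan cannot comply with both.

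The choice matters because withdrawal here may not be random. It is open to patients and relatives, needs no reason and can come after the operation. One arm has a femoral puncture and an aortic balloon in a hybrid room, and the other does not, so the family and the treating team can tell which treatment was given. A haemorrhage, a hysterectomy or a balloon complication could prompt a family to leave, and such events may differ between arms. Removing those patients could create a blood-loss difference or hide one.

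The rule also speaks of withdrawal from the protocol, not of withdrawal of consent. That leaves room to read it as covering patients who leave the assigned procedure, which would widen the conflict.

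**Working it through.** **1. Can both rules hold?** Take a patient who is randomised, operated on, and withdrawn two days later. Under the Statistics section, her EBL, hysterectomy status and operating time enter her assigned arm. Under the Patient withdrawal section, they do not. The values exist, so this is not a missing-data problem; the rule itself removes them.

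**2. The plan's own sample size.** Inputs from the Sample size section: "Considering a difference in volume of bleeding of 1000 ml with a standard deviation of 355 ml", "a difference of 800 ml between two treatment groups is considered to be clinically important", a 2.5% level and 90% power. Read as superiority by a margin with a one-sided 2.5% level, the working difference is 1000 − 800 = 200 ml:

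- n = 2 × [355 × (1.960 + 1.282) / 200]² = 66.2, i.e. 67 per arm, which matches the plan.
- 67 / 0.80 = 83.75, i.e. 84 per arm (168 in total), against the stated 85 (170).

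**3. How many patients the allowance covers.** 0.20 × 85 = 17 per arm and 0.20 × 170 = 34 in total. That leaves 68 per arm, just above the 67 required.

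**4. Worst-case shift.** Assumptions: EBL is normal with SD 355 ml, and a fraction f of one arm is removed, namely those with the highest EBL. With c the (1 − f) quantile and φ the standard normal density, that arm's mean falls by 355 × φ(c) / (1 − f).

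| f | c | φ(c) | Fall in mean |
|---|---|---|---|
| 5% | 1.645 | 0.1031 | 355 × 0.1031 / 0.95 = 38.5 ml |
| 10% | 1.282 | 0.1755 | 355 × 0.1755 / 0.90 = 69 ml |
| 20% | 0.842 | 0.2800 | 355 × 0.2800 / 0.80 = 124 ml |

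**5. Effect on a test of zero difference** (true difference zero, 68 per arm, f = 20%):

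- With SD 355 in both arms, SE = 355 × √(2/68) = 60.9 ml. The probability of a significant result favouring the depleted arm is P(Z > 1.96 − 124/60.9) = 0.53.
- Removing the top values also shrinks the spread in that arm, so the true figure is higher. A simulation with t tests, in which one arm loses its highest values and the other loses equal numbers at random, gives about 10% with 4 lost per arm, 23 to 24% with 8 lost, and 60 to 61% with 17 lost.

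The nominal rate in that direction is 2.5%.

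**6. Power.** For the plan's 200 ml working difference and SD 355, one-sided 2.5%, power is 90.3% with 67 per arm, 90.7% with 68 and 95.7% with all 85. The defect is possible bias; the plan is not short of patients.

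**The case against.** The strongest reply is that the withdrawal rule only respects consent. The sentence before it defines withdrawal by a patient or relative who no longer agrees to take part, and a trial may not use data against a participant's wishes. EBL is measured under general anaesthesia, so a patient cannot react to it during surgery, and the article gives no rate of later withdrawal. If withdrawal is unrelated to arm and outcome, nothing is biased.

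Much of this stands and limits the point. It does not remove the contradiction. Stopping further participation does not by itself require deleting what was already recorded, and the rule deletes it in every case, whether or not the participant asks.

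Four stronger readings are tempting, and the document does not support them.

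- **That the rule removes up to 20% of patients.** The 20% is a planning estimate of dropout. It is neither a cap nor a forecast of withdrawals under this rule, and no limit is stated.
- **That the rule reaches abandoned or changed procedures.** The wording permits this, but the preceding sentence ties withdrawal to consent. It is an ambiguity to close. Hysterectomy for uncontrolled bleeding is part of the traditional arm's described care and so is not withdrawal.
- **That the removed patients might have bled 1000 ml more than those kept, moving the mean by 200 ml.** With a whole-arm SD of 355 ml, the largest gap between any 20% and the other 80% is 355 / √(0.2 × 0.8) = 888 ml for any distribution. That is a shift of at most 0.2 × 888 = 178 ml. Under normality the gap is about 621 ml (124 / 0.2). Setting such a shift against the 800 ml margin would also confuse a test of that margin with a test of zero difference.
- **That the randomised comparison is destroyed.** Bias needs withdrawal related to arm or outcome. The rule allows that but does not show it.

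The absence of a sensitivity analysis for missing EBL is no finding either, because that can be left to the analysis plan.

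**Conclusion.** The point holds: the withdrawal rule is wrong as written, because it contradicts the declared analysis of all outcomes and discards operating-room data already in hand. It should be corrected on the strength of the contradiction alone.

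The figures show what the rule could do, not what it will do. They rest on normal EBL, the plan's SD of 355 ml and removal of exactly the heaviest bleeders in one arm, so they mark the severe end. Even so, four patients lost in this way would raise the false-positive rate in that direction from 2.5% to about 10%. The lack of masking is inferred from the described interventions and from the absence of any masking procedure; the article does not call the trial open-label.

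**What to change.** Replace the sentence that excludes withdrawn patients with:

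> All randomised participants are analysed in the arm assigned. Not receiving or stopping the assigned procedure, or a protocol deviation, is not withdrawal, and in-hospital outcomes continue to be recorded. If consent is withdrawn, data collected up to that point are kept and analysed unless the participant asks for their removal. Withdrawals are reported by arm, with timing and with reasons where given.

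The cost is one paragraph of protocol wording. The main outcomes are already recorded during the admission, no additional patients are needed, and on the plan's own assumptions no power is lost. The Trial status section says recruitment had not begun at publication; if patients have since been enrolled, the change should be made as a dated amendment before any comparison by arm.
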